## Abstract

**Background:**

Venous leg ulcers (VLUs) are the most severe manifestation of chronic venous disease, with long healing time and a high recurrence rate. It imposes a heavy burden on patients, their families, and the health care system. Chronic inflammation triggered by sustained venous hypertension is now recognized as the hallmark of chronic venous disease. The anti-inflammatory effect of pentoxifylline may offer a promising avenue to treat VLUs. However, current evidence of pentoxifylline for VLUs is relatively small and of low quality. The aim of this study is to evaluate the efficacy and safety of pentoxifylline for VLUs in the Chinese population.

**Methods:**

This is a randomized, double-blinded, double-dummy, multi-center, placebo-controlled clinical trial. A total of 240 patients will be randomized to receive pentoxifylline (400 mg, twice daily) or placebo for 24 weeks. All participants will receive diosmin treatment and standard care of VLUs and other comorbidities. The primary outcome is the difference in the wound healing rate within 12 weeks between pentoxifylline and placebo. Secondary outcomes include (1) percent wound size changes at 12 weeks, (2) the levels of TNF-α and IL-6, (3) venous clinical severity score and chronic venous insufficiency quality of life score, and (4) ulcer recurrence within 24 weeks.

**Discussion:**

This study would evaluate the efficacy and safety of pentoxifylline for VLUs in the Chinese population. If confirmed, it wound offer another effective and safe therapeutic option for treatment of VLUs.

**Trial registration:**

The trial was registered at the Chinese Clinical Trial Registry (No. ChiCTR-2100053053). Registered on 10 November, 2021, https://www.chictr.org.cn/showproj.aspx?proj=137010

## Background

Chronic venous disease (CVD) is a common pathology of the circulation system and is characterized by symptoms and signs as a result of structural or functional abnormalities of the veins. The most common symptoms and signs include pain, tightness, heaviness, feeling of swelling, reticular and varicose veins, edema, skin changes such as pigmentation, or ulceration [1]. CVD is often overlooked by healthcare providers because of an under-appreciation of the magnitude and impact of the problem, as well as incomplete recognition of the manifestations. In fact, CVD is a very common problem. A global survey suggested that the worldwide prevalence of CVD is 83.6%, with 63.9% of the subjects ranging from C1 to C6 [2]. In China, the prevalence of CVD is 8.89%, that is, there are nearly 100 million patients. The annual incidence rate is 0.5% to 3.0% [3].

Venous leg ulcers (VLUs) are defined as ulcers of the leg or foot that occur in the presence of venous disease. VLUs are the most severe manifestation of CVD. VLUs represent 80% of all leg ulcers [4]. The prevalence of VLUs is 1.5% in the general population in China [3], with a higher prevalence in the elderly [4]. Furthermore, VLUs are characterized by slow healing time and a high recurrence rate [5]. With the advent of global aging, more populations will be affected by VLUs. VLUs impose a heavy burden on patients’ physical and mental health and substantially reduce their quality of life. In addition, VLUs impose a heavy socioeconomic burden on patients, their families, and the health care system. Therefore, it is imperative to take efforts to improve the management of VLUs.

The main pathophysiology of VLUs is venous reflux or obstruction, venous hypertension, and chronic inflammation [6]. Conservative management is often the initial choice to reduce symptoms and protect against the progression of CVD. Given the severity and anatomic disorders of CVD, surgical and interventional methods are often reserved for unsatisfactory responses to conservative measures. Compression therapy is the mainstay of CVD [7]. Compression therapy can significantly improve symptoms and signs such as pain, swelling, skin pigmentation, activity, and well-being. For patients with ulcers, the benefits of long-term compression therapy have been repeatedly demonstrated in randomized trials. A healing rate as high as 97% can be achieved in those who are compliant with therapy [8].

In addition, pharmacological treatment could be an option. Venoactive drugs include flavonoids (diosmin), aescin, and coumarins. The main principle of these drugs is to improve venous tone, capillary permeability, lymphatic drainage, and muscle pump function. These drugs could provide relief of pain and swelling or accelerate venous ulcer healing. The nonvenoactive drug sulodexide has also been used to treat VLUs effectively [9]. In recent years, it has been increasingly recognized that chronic inflammation, possibly triggered by sustained venous hypertension, is the principal basis that potentiates the disease progression of CVD. Chronic inflammation of the venous vessel wall could lead to degradation of venous integrity and function, resulting in diminished venous return, fluid accumulation, tissue fibrosis, atrophy, and ulceration in severe cases [10].

Pentoxifylline is used as a drug to treat peripheral artery disease and has been used in the treatment of VLUs. It could inhibit the synthesis of inflammatory mediators, decrease cytokine release, and suppress leukocyte function [11]. The anti-inflammatory effect of pentoxifylline may offer a promising avenue to treat VLUs. In fact, there have been several trials suggesting that pentoxifylline could improve the healing rates of VLUs. In a meta-analysis of 13 randomized clinical trials, pentoxifylline significantly improved the ulcer healing rate and time to healing of VLUs [12].

In addition, other possible mechanisms of pentoxifylline might improve wound healing [13]. Briefly, pentoxifylline could increase cAMP levels in the smooth muscle of vessels, increase erythrocyte flexibility, and then improve microcirculation and oxygen delivery [14]. The fibrinolytic property might degrade microcirculation fibrin, improve skin and subcutaneous nutrition, and then improve wound healing [15].

However, the evidence that currently recommends the use of pentoxifylline in VLUs is relatively weak. Furthermore, none of the trials were carried out in China. Thus, it is imperative to investigate the efficacy and safety of pentoxifylline for VLUs in the Chinese population. Therefore, we designed a multi-center, randomized, double-blinded, placebo-controlled clinical trial to evaluate the efficacy and safety of pentoxifylline in the Chinese population for the treatment of VLUs.

## Methods and design

### Objective

The main aim of this study is to investigate the efficacy and safety of pentoxifylline for VLUs in the Chinese population.

### Study design

This is a multicenter, randomized, double-blinded, double-dummy, placebo-controlled clinical trial. The study was registered at the Chinese Clinical Trial Registry (No. ChiCTR-2100053053). Eligible participants will be randomly allocated to either pentoxifylline or placebo at a ratio of 1:1. The flow chart of this trial is briefly shown in Fig. 1. The protocol was designed according to the Standard Protocol Items: Recommendations for Interventional Trials (SPIRIT) 2013 Statement [16].

**Fig. 1 Fig1:**
[figure not shown]
Flow chart of the pentoxifylline clinical trial

### Study population

Recruitment of patients with VLUs will be conducted at thirteen hospitals in China (Table 1). All patients seeking treatment of VLUs in these hospitals will be screened according to the inclusion and exclusion criteria. Once written consent is obtained and the inclusion criteria is confirmed, participants will be enrolled in this trial. This trial will begin in August 2022 and will continue until October 2024.

**Table 1 Tab1:** The hospitals participating in this study

Number	Participating hospitals
1	West China hospital, Sichuan University
2	Sichuan Provincial People’s Hospital
3	Shanxi Bethune Hospital
4	Liyuan Hospital of Tongji Medical College of Huazhong University of Science & Technology
5	Zhu Xianyi Memorial Hospital of Tianjin Medical University
6	Tianjin First Central Hospital
7	China-Japan Union Hospital of Jilin University
8	Shandong Provincial Hospital
9	The Affiliated Hospital of Shandong University of Traditional Chinese Medicine
10	The Affiliated Hospital of Qingdao University
11	The Second Affiliated Hospital Zhejiang University School of Medicine
12	Jiangsu Province Hospital
13	Nanfang Hospital, Southern Medical University

### Diagnostic criteria of VLUs

VLUs are defined as ulcers of the leg or foot that occur in the presence of venous disease. CEAP classification is a widely accepted tool to diagnose CVD [17]. The name CEAP classification stands for Clinical (C), Etiological (E), Anatomical (A), and Pathophysiological (P). VLUs is the most advanced form of CVD [18]. In this trial, CEAP was used to assist the diagnosis of VLUs.

### Inclusion criteria

To be eligible to participate in this study, a subject must meet all of the following criteria:Age ≥ 18 yearsMeeting the criteria of VLUs (patients with CVD and complicated with ulcers (level C6 of CEAP classification). The surface area of the VLU should be within the range of 1 cm^2^ and 20 cm^2^. If there are more than one ulcer in a subject, the ulcer with the largest area will be chosen as the index ulcer. The distance between the index ulcer and other ulcers should be more than 2 cm.Consciousness, without aphasia, able to eat drugsAnkle brachial index ≥ 0.7Written informed consent by participants or surrogate

### Exclusion criteria

A potential subject who meets any of the following criteria will be excluded from this trial:Ulcers of other etiologies, such as sickle cell anemia, necrobiosis lipoidica, pyoderma gangrenosum, lower extremity artery disease, and vasculitisKnown malignancies, or immune deficiency diseaseSevere infectionKnown pregnancy or lactation, or patients who anticipated becoming pregnantAllergy to pentoxifylline or methylxanthinesGangrene of ulcersLower extremity edema caused by cardiac, hepatic, or renal diseaseKnown severe disorder of heart, liver, kidney or hematopoietic system (ALT more than 2.5 times upper limit of normal, AST more than 2.5 times upper limit of normal, or creatine more than 1.5 times upper limit of normal)Known acute cardiac infarction, severe coronary artery disease, cerebral arteriosclerosis, hypertension, or severe arrhythmiaKnown cerebral hemorrhage, subarachnoid hemorrhage, retinal hemorrhage, hemorrhagic stroke, bleeding tendency (for example, long-term use of anticoagulant drugs), or history of recent bleeding

### Withdrawal of individual subjects

Subjects can leave the study at any time for any reason. The trial should be suspended in a special subject in the following conditions: (1) serious adverse events relevant or not relevant to pentoxifylline occur, (2) suffer from acute life-threatening disease, (3) death, and (4) violate the trial protocol, which influenced the evaluation of the endpoint.

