### Interventions

All patients will receive standard care of VLUs including compression therapy, sclerotherapy, and endovenous and surgical management. Other standard management such as treatment of infection, debridement, local wound care, anti-inflammatory analgesic drugs, dressings, and metabolic management will be prescribed as appropriate. Current guidelines were followed as per the attending clinician’s judgment [3, 5].

After randomization, participants will be given either pentoxifylline 400 mg twice daily or matched placebo (simulation agent of pentoxifylline) for 24 weeks. Because the dosage of pentoxifylline was 400 to 800 mg per day on the label of pentoxifylline in China, the dose in the trial was 400 mg twice a day. The micronized purified flavonoid fraction (90% diosmin and 10% other flavonoids) is currently one of the most widely accepted effective drugs for CVD and is also recommended by guidelines [17]. Thus, all patients in both groups will be dosed 450 mg diosmin twice daily for 24 weeks. Participants are prohibited from using fibrinolytic drug sulodexide and other venoactive drugs, such as aescin (horse chestnut extracts), coumarins, and low molecular weight heparin. All participants will be required to return the drug tablet to monitor the adherence. There will be no special criteria for discontinuing or modifying allocated interventions.

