### Outcomes

#### Primary outcome

Wound healing rate within 12 weeks, expressed as the proportion of participants with complete wound healing of the index ulcer within 12 weeks. Complete wound healing is defined as full epithelialization of the wound without scarring [19].

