### Data analysis

An independent statistical analysis plan will be formulated. All analyses will be conducted in the full analysis set (FAS) population, defined as all patients randomized to an intervention group having at least one efficacy treatment after randomization. The outcomes will also be assessed in the per-protocol set (PPS). The results from FAS and PPS will be compared. Safety set will be used to evaluate the safety of experimental drug. The compliance of treatment and treatment-related withdrawals will be evaluated by arm. Participants’ characteristics and clinical measures will be described as the mean ± standard, median (interquartile range), or frequencies and percentages as appropriate. All statistical analyses will be performed using SAS, V.9.4. All statistical tests are bilateral tests. A *p* value ≤ 0.05 is considered statistically significant.

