### Analysis of efficacy

The primary analysis will aim to compare the wound healing rate within 12 weeks between the pentoxifylline group and the control group by chi-squared test or Fisher’s exact test. The result will be expressed as risk ratio and 95% confidence interval. The wound healing rate at 4, 8, 16, and 24 weeks will be assessed by time-event analysis. Kaplan–Meier plot, Log-rank test, and Cox regression will also be used to analysis the time-to-event outcome, with the result of hazard ratio and 95% confidence interval. The covariates that should be adjusted in the Cox regression analysis include gender, age, duration of disease, BMI, pre-treatment ulcer area, compression therapy, and endovenous surgery. Last observation carried forward will be used to fill up the missing values if some primary outcomes may be missing.

The secondary analysis will compare the VCSS score, CIVIQ score, percent of wound size changes, and ulcer recurrence within 24 weeks by *t* test, Wilcoxon rank test, chi-squared test, or Fisher’s exact test as appropriate.

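### The withdrawal rule conflicts with the statement that there are no discontinuation criteria and, on its natural reading, ends ulcer assessment after serious adverse events and some protocol violations

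*Protocol article*

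**What the plan says.** All references are to the protocol article.

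- *Withdrawal of individual subjects*: "The trial should be suspended in a special subject in the following conditions". Four conditions follow. The first is that "serious adverse events relevant or not relevant to pentoxifylline occur"; the second and third are acute life-threatening disease and death; the fourth covers subjects who "violate the trial protocol, which influenced the evaluation of the endpoint".
- *Interventions*: "There will be no special criteria for discontinuing or modifying allocated interventions".
- *Primary outcome*: "the proportion of participants with complete wound healing of the index ulcer within 12 weeks".
- *Data analysis*: "All analyses will be conducted in the full analysis set (FAS) population". Membership of that set extends to "all patients randomized to an intervention group having at least one efficacy treatment after randomization". A per-protocol set is analysed as well, and the two results are compared.
- *Analysis of efficacy*: "Last observation carried forward will be used to fill up the missing values if some primary outcomes may be missing".

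The total follow-up is 24 weeks (*Follow-up*), and healing is also reported at weeks 4, 8, 16 and 24 (*Secondary outcomes*).

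**The concern.** There are two linked problems.

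First, the two sections cannot both be followed as written. Ending the trial in a participant also ends the allocated intervention. One section lists conditions that require this, and the other says there are no special criteria for it. Thirteen hospitals could apply different rules.

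Second, the withdrawal section treats stopping the drug and leaving the study as one event. Serious adverse events and endpoint-affecting violations both arise after randomisation. Serious adverse events may differ by arm, and a serious adverse effect permits unblinding (*Randomization and allocation concealment*). Use of a prohibited venoactive drug is plausibly more likely when an ulcer is doing badly. If such participants are no longer assessed, missing outcomes are tied to treatment and ulcer course. The carried-forward value then replaces an outcome that could have been observed.

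**Working it through.** **1. The text.** The withdrawal section's heading, its opening sentence about leaving the study and the presence of death in the list all favour exit from the trial over a pause in study drug. The *Interventions* statement carries no cross-reference to that list. On either meaning of suspension, conditions that stop the allocated drug exist in one section and are denied in the other.

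**2. One participant under the stated rules.** Someone is removed at, say, week 6 with an open ulcer. They have been randomised and treated, so they remain in the full analysis set. No week 12 status is observed. The last observation is an open ulcer, so they count as not healed. Someone whose ulcer had closed before removal already has the outcome and counts as healed.

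**3. The plan's own figures.** *Sample size* gives healing rates of 62.7% and 40.6%, 5% significance, 80% power, 190 evaluable and 240 in total after 20% drop-out. The drop-out step gives 190/0.80 = 237.5, so 238 against the stated 240. The 190 is not reproduced: the two-sided normal approximation for two proportions gives 160 (80 per arm), or 176 with continuity correction. That is a separate matter. It matters here only because 240 fully followed participants then have more than 80% power.

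**4. Illustration.** Inputs: n = 120 per arm (240 at 1:1) and the planning rates. The removal shares d are assumptions, because the document gives only 20% drop-out overall. It is also assumed that nobody removed had already healed, and that those removed would otherwise have healed at their arm's average rate.

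- Scored healing rate in an arm: p × (1 − d)
- SE0 = √[2p̄(1 − p̄)/n], where p̄ is the mean of the two scored rates
- SE1 = √[(pA(1 − pA) + pB(1 − pB))/n]
- Power = Φ[(pA − pB − 1.96 × SE0)/SE1]

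Worked case, 20% removed on pentoxifylline and 10% on placebo: 0.627 × 0.8 = 0.5016; 0.406 × 0.9 = 0.3654; difference 0.1362; ratio 1.373. With p̄ = 0.4335, SE0 = 0.0640 and SE1 = 0.0634, power = Φ(0.17) ≈ 0.57.

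| Removed, pentoxifylline / placebo | Scored healed | Difference (points) | Risk ratio | Power |
|---|---|---|---|---|
| 0% / 0% | 62.7% / 40.6% | 22.1 | 1.54 | 93.4% |
| 10% / 10% | 56.4% / 36.5% | 19.9 | 1.54 | 87.5% |
| 20% / 20% | 50.2% / 32.5% | 17.7 | 1.54 | 79.8% |
| 20% / 10% | 50.2% / 36.5% | 13.6 | 1.37 | 56.8% |
| 5% / 15% | 59.6% / 34.5% | 25.1 | 1.73 | 97.7% |

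With no true effect (40.6% in both arms), counting rejections in either direction: 20% / 10% gives a risk ratio of 0.89 and a type I error of 10.1%; 5% / 15% gives 1.12 and 10.0%.

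**5. The other extreme.** If everyone removed would not have healed anyway, scoring them not healed is correct. The rates stay at 62.7% and 40.6%, and there is no bias.

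**The case against.** The strongest objection is that the verb in the withdrawal section is ambiguous. If it means suspension of study drug only, assessments may continue and no outcome need be missing. *Adverse events* provides follow-up through 12 months after treatment starts, so contact after an event is foreseen, at least for safety. The article condenses a fuller protocol, and the schedule in Fig. 2 was not available to me. Silence on continued assessment would therefore not be a finding in itself. This stands as a limit on the missing-data part. It does not remove the conflict with *Interventions*, which exists on either meaning.

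It can also be said that no special criteria means none beyond the general withdrawal list. That is possible, but the text does not say so, and a site would have to guess.

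Three stronger readings are tempting, and the document does not support them.

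- A reader might infer that removing violators turns the full analysis set partly into a per-protocol set. It does not: the definition keeps everyone randomised and treated. Any bias enters through the carried-forward value, not through exclusion.
- A reader might infer that anyone removed before week 12 has no primary outcome. Healing is counted within 12 weeks, so earlier healing is retained.
- A reader might infer that the rule costs a known amount of power, or works against pentoxifylline. The 57% comes from one assumed imbalance. If violations follow poor healing and the drug works, more removals could fall on placebo, and those removed would largely be true non-healers. With 20% lost in each arm, power is 79.8%, essentially the planned level. Blinding also limits differential removal for violations.

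Death is in the list, but outcomes lost to death are unavoidable and are no fault of the design.

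**Conclusion.** The point holds in a limited form. The conflict between *Withdrawal of individual subjects* and *Interventions* is textual and rests on no assumption. The two must be reconciled; which rule governs stopping of study drug is a clinical decision for the sponsor.

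The statistical consequence holds on the natural reading of the withdrawal section, that the participant leaves the trial. The plan then creates avoidable missing outcomes after randomisation and fills them as not healed for anyone with an open ulcer. Their frequency can depend on arm and ulcer course.

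Neither the size nor the direction of the bias can be derived from the document. Under the assumed shares above, the risk ratio ranges from 1.37 to 1.73 around the planned 1.54, and type I error is about 10% where removal differs by 10 points between arms. If those removed would not have healed anyway, there is no bias. The change is worth making because it is cheap and prevents the problem.

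**What to change.** 1. Reconcile the two sections on when study drug is stopped, and separate stopping study drug from leaving the study.
2. State that every randomised participant, whatever the treatment status or protocol deviation, stays in follow-up and has the index ulcer assessed at the scheduled visits, including weeks 12 and 24, unless consent is withdrawn.
3. State that protocol violations determine membership of the per-protocol set only and do not end outcome collection. The plan already has that set, so no information is lost.

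The cost is a wording amendment and already scheduled visits kept for a few more participants. The sample size and the planned tests are unchanged. Fewer outcomes would need to be filled by last observation carried forward.

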### Informed consent

Written informed consent will be obtained from all participants at each participating center or their legal representative if they are unable to provide consent. On the consent form, participants will be asked whether they agree to the use of their data if they opt out of the trial. Participants will also be asked for permission for the research team to share relevant data with people from the universities taking part in the research or from regulatory authorities, where relevant. Clinical trial liability insurance will be purchased for participants during the trial treatment period. After the trial ended, trial participants will still have access to their attending doctors. Because there is no anticipated harm, no compensation for trial participation will be provided. Informed consent materials of Chinese version (not in English) are available, on request, from the corresponding author.

